### Data management

Study data will be collected and managed using REDCap (Research Electronic Data Capture) electronic data capture tools hosted at the Clinical Trials Unit (CTU) at the University Hospital of Bern.^33^^,^^34^ REDCap is a secure, Web-based software platform designed to support data capture for research studies, providing (1) an intuitive interface for validated data capture; (2) audit trails for tracking data manipulation and export procedures; (3) automated export procedures for seamless data downloads to common statistical packages; and (4) procedures for data integration and interoperability with external sources. The case report forms are implemented electronically. All electronic data are encrypted, password protected and stored on a secure network at the CTU of the University of Bern. Regular evaluations of data integration and quality, management and resolution of data discrepancies, tracking of adverse event information and database quality control will be performed. At the conclusion of the study, the CTU Bern will lock the clinical data and perform the final analysis of the trial results.

### Statistical analysis

A statistician, who is blinded to treatment allocation, will perform analyses. The principal investigators will have full access to the data and will vouch for the data and the analysis. Analyses are conducted according to the intention-to-treat principle meaning that patients are analyzed based on the treatment arm to which they were originally allocated. The primary analysis is in the per-protocol population with confirmatory testing in all the randomized patients, in both these populations using the intention-to-treat principle. Hence, noninferiority will only be claimed for the FARAPULSE PFA catheter if the analysis in both populations show that the upper limit of the confidence interval of the rate ratio using Mantel-Cox time to first recurrence of any atrial tachyarrhythmia between days 91 and 365 postablation comparing FARAPULSE vs Arctic Front does not cross 20% (rate ratio of 1.2), using a 1-sided test with alpha of 5%.

The per-protocol population is defined as all patients in which (1) the randomized device was used to initiate the ablation (irrespective of whether this ablation was completed successfully, or whether a second device was used to complete the ablation) and (2) none of the inclusion and exclusion criteria were breached.

Primary analysis will take place after all patients have completed 1-year follow-up. For the primary analyses (FARAPULSE vs Arctic Front), unadjusted survival curves are estimated by the Kaplan-Meier method and compared by log rank tests. Unadjusted rate ratios and confidence intervals for rate ratios are derived from Mantel-Cox models. The proportional hazards assumption is assessed by visual inspection of the log-negative-log plot and through a formal test of the interaction term group × time at an alpha of 0.05. Secondary endpoints expressed as time to event are analyzed similarly using Kaplan-Meier survival curves and a log-rank test. All tests are conducted at an alpha level of 0.05. Basic assumptions are verified prior to analysis. In case of noninferiority for the primary endpoint, a superiority analysis is performed using a 2-tailed significance alpha level of 0.05.

Comparisons between the 2 treatment groups are performed using demographic, clinical, procedural, and imaging characteristics, and tested if postrandomization. Continuous variables are presented as mean ± SD or median and interquartile range depending on their distribution. Categorical variables are stated as number and proportion. Characteristics are compared between the 2 treatment groups by means of unpaired *t* tests for continuous variables and chi-square tests or Fisher’s exact tests for categorical variables and reported *P* values will be 2-sided. If a normal distribution cannot be assumed, nonparametric tests are considered to compare patient characteristics.

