### Sample size

Using continuous ICM data, the occurrence of the primary endpoint is expected at 40% based on the data from the recent Cryoballoon or Radiofrequency Ablation for Atrial Fibrillation Assessed by Continuous Monitoring: A Randomized Clinical Trial study,^31^ and the Cryoballoon or Radiofrequency Ablation for Paroxysmal Atrial Fibrillation trail.^32^ With a sample size of 99 per group and a 1-sided 0.025 significance level, the study will have 80% power (using log-rank test) with the noninferiority margin set to 20% comparing the 2 single-shot ablation technologies. This noninferiority margin and power is identical to the noninferiority margin in the Cryoballoon or Radiofrequency Ablation for Atrial Fibrillation Assessed by Continuous Monitoring: A Randomized Clinical Trial study, which is one of the most highly cited articles on AF ablation in recent years and may be considered relevant and representative of our field.^31^ The upper limit of the 2-sided 95% confidence interval for the difference in the cumulative incidence comparing the FARAPULSE PFA catheter vs the Arctic Front cryoballoon had to exclude 1.2 times the percentage points of the cumulative incidence in the control device (Artic Front) for the primary outcome to define noninferiority of the experimental device (FARAPULSE). In accordance with the Food and Drug Administration regulations, the noninferiority hypothesis was tested using a 1-sided alpha of 0.025, which corresponds to a 2-sided alpha of 0.05.

Factoring in a 5% loss to follow-up, 105 patients per group will be randomized, resulting in a total study population of 210 (Supplemental Table 4).

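### The noninferiority margin is stated on incompatible scales, and under the written rule (rate ratio 1.2) power is about 13% or 20%, depending on the alpha used, not the stated 80%

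*Protocol article*

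**What the plan says.** The protocol article gives the confirmatory criterion in three forms.

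- **Sample size, margin and power.** At 40% expected recurrence, 99 per group and 1-sided 0.025, "the study will have 80% power (using log-rank test) with the noninferiority margin set to 20% comparing the 2 single-shot ablation technologies". The scale of the 20% is not given.
- **Sample size, criterion.** The upper limit of the 2-sided 95% confidence interval for the difference in cumulative incidence "had to exclude 1.2 times the percentage points of the cumulative incidence in the control device (Artic Front) for the primary outcome". The same paragraph repeats that noninferiority is tested at 1-sided 0.025.
- **Statistical analysis, decision rule.** Noninferiority is claimed only if, in both the per-protocol and the all-randomized populations, the upper confidence limit of the Mantel-Cox rate ratio "comparing FARAPULSE vs Arctic Front does not cross 20% (rate ratio of 1.2"). This sentence sets a 1-sided alpha of 5%.

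The Sample size section also says that the margin and power match those of an earlier cited trial, and it refers to Supplemental Table 4.

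**The concern.** A difference of 20 percentage points, a relative increase of 20% in cumulative incidence and a rate ratio of 1.2 are three different amounts of permitted loss. At 40% control recurrence they allow 20, 8 and about 5.8 points. The power statement can belong to only one of them, and the sentence that governs the claim uses the strictest.

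The trial's main conclusion therefore depends on which sentence is followed. An observed rate ratio of 0.95, slightly in favour of the new device, would fail the 1.2 rule. With about 79 events its upper limit would be 0.95 × exp(1.96 × 0.225) = 1.48, or 0.95 × exp(1.645 × 0.225) = 1.38 at 1-sided 5%. Under the 20-point rule, equally effective devices would pass about four times in five. If the conflict is settled after results are known, the margin will have been chosen with the answer in view.

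**Working it through.** **Inputs (Sample size and Statistical analysis sections).** Recurrence 40%; 99 per group, 105 after a 5% allowance for loss; 1-sided 0.025 for sizing and 1-sided 5% in the decision rule; 80% power; log-rank test. Assumption: the true rate ratio is 1, since the article gives one recurrence rate and assumes no benefit.

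**Step 1: reproduce the stated sample size.** Take the margin as 20 absolute points, 40% versus 60%.

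- Hazard ratio at the margin: ln(0.40)/ln(0.60) = 1.794.
- Freedman events: (1.960 + 0.842)² × [(1.794 + 1)/(1.794 − 1)]², about 97.2, so 98. At a mean event probability of (0.40 + 0.60)/2 = 0.50 this is 98 per group, against 99 stated. Power at 99 per group is 80.7% (Schoenfeld: 82.8%).
- Check on proportions: SE = √(2 × 0.40 × 0.60/99) = 0.0696; power = Φ(0.20/0.0696 − 1.96) = 81.9%.
- Loss allowance: 99/0.95 = 104.2, so 105, as stated.

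The stated design is reproduced on the absolute 20-point reading.

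**Step 2: power under a rate ratio of 1.2.** Expected events are 2 × 99 × 0.40 = 79.2, so SE(log ratio) = 2/√79.2 = 0.225. With 105 per group there are 84 events and SE = 0.218.

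- 1-sided 0.025: Φ(ln 1.2/0.225 − 1.96) = 12.5% with 79.2 events; 13.0% with 84.
- 1-sided 5%: Φ(ln 1.2/0.225 − 1.645) = 20.2% with 79.2 events; 20.9% with 84.
- A log-rank simulation with 20,000 replicates agrees: 12.6% and 13.1% at 0.025; 20.4% and 20.7% at 5%.
- Largest observed ratio that still passes, with 79.2 events: 1.2 × exp(−1.96 × 0.225) = 0.77 at 0.025; 1.2 × exp(−1.645 × 0.225) = 0.83 at 5%.
- Events for 80% power: 4 × (1.960 + 0.842)²/(ln 1.2)² gives 945, about 1,182 per group at 40% recurrence. At 1-sided 5% it is 744 events, about 930 per group.

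**Step 3: relative factor of 1.2 on incidence.** The margin is 0.48 − 0.40 = 0.08. Power = Φ(0.08/0.0696 − 1.96) = 20.9% at 0.025, and 31.0% at 1-sided 5%. About 589 per group would be needed for 80% power at 0.025.

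**Side by side, 40% control recurrence, 99 per group, 1-sided 0.025:**

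| Reading of the margin | Incidence at the margin | Difference | Hazard ratio | Power |
|---|---|---|---|---|
| 20 absolute points | 60% | 20 points | 1.79 | 81–83% |
| 1.2 × control incidence | 48% | 8 points | 1.28 | 21% |
| Rate ratio 1.2 | 1 − 0.6^1.2 = 45.8% | 5.8 points | 1.20 | 12.5% |

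**The case against.** **The three statements may be one relative margin, loosely worded.** That is a fair reading of the intention: 20%, a factor of 1.2 and a rate ratio of 1.2 resemble each other. It does not help, because neither relative version comes near 80% power with 99 per group.

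**The decision rule uses a 1-sided alpha of 5%.** This stands. The 13% figure is the like-for-like comparison with the 80% claim, which was made at 0.025. For the decision rule exactly as written, power is about 20%. A reader might infer that 13% is the power of that sentence as it stands, but its own alpha does not support this.

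**The new device may be better.** The article says that improved efficacy is an aim, but the sizing assumes no benefit. If the true ratio were 0.75 (an assumption), the new-device incidence would be 1 − 0.6^0.75 = 31.8%. Events would be 99 × (0.400 + 0.318) = 71.1, and power roughly 51% at 0.025 or 63% at 5%, still below 80%.

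**Unseen material may settle the scale.** The cited trial and Supplemental Table 4 are not shown, and either might say whether 20% is absolute. That is a reason not to declare which margin was meant. It does not remove the conflict between two sections of the same article.

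**A stronger reading of the Sample size criterion.** Taken literally, 1.2 times the control incidence as a limit on a difference is 1.2 × 40 = 48 points, and a reader might infer that a clearly worse device could pass. No other sentence points to so wide a limit, and the decision rule contradicts it. It is best treated as a wording error in that sentence.

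**Conclusion.** The point holds. The margin is not stated on one scale, and the 80% power does not belong to the written decision rule. Under a rate ratio of 1.2, power is about 13% at 1-sided 0.025 and about 20% at 1-sided 5%, assuming equal devices and 40% recurrence in both arms. Requiring both populations to pass cannot raise these figures. The relative reading on incidence gives about 21% at 0.025.

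The 20-point reading is inferred from the arithmetic: no sentence says 20 percentage points. A reader might conclude that 20 points is therefore the right margin and that 1.2 is a slip. The documents show only which margin was used for sizing, not which one the sponsor intended for the claim.

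**What to change.** Before any unblinded data are seen, state one margin, one scale and one alpha in identical terms in the Sample size and Statistical analysis sections.

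- **If the sizing margin is the intended one:** claim noninferiority when the upper limit of the 2-sided 95% confidence interval for the Kaplan-Meier difference in cumulative incidence at day 365 (FARAPULSE minus Arctic Front) is below 20 percentage points in both populations. Report the rate ratio descriptively. Delete the rate ratio of 1.2 and the 5% alpha from the Statistical analysis section, and the 1.2-times wording from the Sample size section. Say openly that this is much more lenient than a rate ratio of 1.2, and justify it.
- **If a rate ratio of 1.2 is intended:** keep it, choose the alpha, correct the Sample size wording, and restate the power as about 13% (1-sided 0.025) or about 20% (1-sided 5%).

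**Cost.** Neither route needs more patients. The first is nonetheless a substantive relaxation of the written primary criterion and should be documented as such. The second means accepting low power. Keeping 1.2 and also 80% power would take about 1,182 per group at 0.025, or about 930 at 5%, before any allowance for loss.

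### The noninferiority test is set at 1-sided 0.025 in the sample-size section but at 1-sided 5% in the rule for claiming noninferiority

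*Protocol article*

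**What the plan says.** The Sample size section fixes the level in three places, and they agree:

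- The calculation: "With a sample size of 99 per group and a 1-sided 0.025 significance level, the study will have 80% power (using log-rank test").
- The interval to be used: "The upper limit of the 2-sided 95% confidence interval for the difference in the cumulative incidence".
- The test, which the article attributes to regulatory requirements: "the noninferiority hypothesis was tested using a 1-sided alpha of 0.025, which corresponds to a 2-sided alpha of 0.05".

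The Statistical analysis section then gives the operative rule. Noninferiority is claimed only if, in both the per-protocol population and all randomized patients, the upper confidence limit of the Mantel-Cox rate ratio stays below 1.2, "using a 1-sided test with alpha of 5" percent. The confidence level of that interval is not given. Two further sentences in the same section bear on the level: "All tests are conducted at an alpha level of 0.05", with no sidedness, and, once noninferiority is shown, "a superiority analysis is performed using a 2-tailed significance alpha level of 0.05".

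**The concern.** A 1-sided test at 0.025 and a 1-sided test at 0.05 are different tests of the same hypothesis. The first compares the upper limit of a 2-sided 95% interval with the margin, the second the upper limit of a 2-sided 90% interval. The looser level stands in the sentence that decides whether noninferiority is claimed, and the stricter one in the section that justifies the sample size.

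At stake is the type I error of the trial's main confirmatory claim. An analyst who follows the analysis section accepts twice the nominal error that the sample-size section says is controlled. If the result falls between the two limits, either conclusion can be defended from the text, and in an open-label trial the choice of rule could be made after the data are seen.

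**Working it through.** **1. Which level does the stated sample size rest on?**

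Inputs from the Sample size section: "the occurrence of the primary endpoint is expected at 40" percent, 80% power, 99 per group, 5% loss, and a margin of 20%. For this step only, the margin is read as percentage points (40% against 60%), the reading that reproduces the stated number.

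- Hazard ratio for 60% against 40% under proportional hazards: ln(0.4)/ln(0.6) = 1.794.
- Freedman events for the log-rank test: (z_α + z_β)² × [(HR + 1)/(HR − 1)]².
- At 1-sided 0.025: (1.960 + 0.842)² × (2.794/0.794)² = 7.85 × 12.39 = 97.2, so 98 events. At an average event proportion of 50%, that is 98 patients per group, against 99 stated.
- At 1-sided 0.05: (1.645 + 0.842)² × 12.39 = 76.6, so 77 events and 77 patients per group.
- Loss to follow-up: 99/0.95 = 104.2, so 105 per group, as stated.

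Comparing two proportions, 40% against 60%, gives 97 per group at 1-sided 0.025 and 77 at 1-sided 0.05. The stated 99 therefore matches the level that the section names.

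**2. Nominal error under the analysis-section rule**

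The rule compares the upper limit of the rate ratio with 1.2, so its error is evaluated at a true ratio of 1.2.

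- Upper limit of a 2-sided 95% interval (z = 1.960): 2.5%.
- Upper limit of a 2-sided 90% interval (z = 1.645): 5.0%, a ratio of 0.05/0.025 = 2.

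A simulation of 10,000 trials (Cox model, true hazard ratio 1.2, 99 per group, 40% events in the control group) gave 2.4% and 4.8%.

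**3. Results on which the two rules disagree**

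Assumption: 40% of 2 × 99 = 198 patients have an event, so about 79 events.

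- SE of the log ratio ≈ 2/√79.2 = 0.225.
- Largest observed ratio that passes = exp(ln 1.2 − z × SE), with ln 1.2 = 0.182.
- At 1-sided 0.025: exp(0.182 − 1.960 × 0.225) ≈ 0.77.
- At 1-sided 0.05: exp(0.182 − 1.645 × 0.225) ≈ 0.83.

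With all 210 patients contributing (84 events, SE = 2/√84 = 0.218), the limits become about 0.78 and 0.84, so the band hardly moves.

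If the two devices were truly equal and there were 79 events, the chance of passing is 12.5% at 1-sided 0.025 and 20.2% at 1-sided 0.05. The chance of landing in the disputed band is then 20.2% − 12.5% = 7.7%.

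**The case against.** The best defence is that this is a slip of sidedness. The Sample size section itself equates 1-sided 0.025 with 2-sided 0.05, and the 5% may have been carried into the analysis section with the wrong label. The 2-tailed 0.05 set for superiority points the same way. That is probably what happened, but it does not remove the contradiction: the sentence says 1-sided, it is the decision rule, and the general statement on alpha gives no sidedness that would correct it.

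A second objection is that noninferiority must be shown in both populations, so the true error is at most the nominal level under either reading. This stands: the doubling is of the nominal rate per test. The per-protocol and all-randomized sets should overlap heavily, so the ratio of the true rates should stay close to 2.

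A third is that one unusual combination at 1-sided 0.05 (77 events divided by a 40% event proportion in both arms, about 96 per group) also comes near 99. It does, but the article ties 99 to 0.025 in so many words.

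Two stronger readings are tempting and are not supported.

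- A reader might put the consequence on the percentage-point scale: a false-claim rate of 5.0% instead of 2.5% at 60% against 40%, and a flipped conclusion for an observed excess of 6.4 to 8.5 points (0.20 − z × √(0.48/99)). The analysis-section rule is on the rate ratio. At 60% against 40% the hazard ratio is about 1.79. With about 99 events (SE about 0.20), the chance of a false claim under that rule is about 0.004% at 1-sided 0.025 and 0.013% at 1-sided 0.05. An observed excess of 6.4 to 8.5 points puts the ratio above 1, and it fails at either level.
- A reader might also infer that the follow-on superiority test is compromised. It is not: it keeps its own 2-sided 0.05 level, and a looser noninferiority step does not raise that test's error. It is only evidence of the level intended.

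**Conclusion.** The contradiction is real and unreconciled. The sample-size section fixes 1-sided 0.025 and the stated 99 per group rests on it; the rule for claiming noninferiority uses twice that level. The factor of two in nominal error follows from the two levels alone, whatever the scale of the margin. The disputed band of observed ratios, about 0.77 to 0.83, rests on the 1.2 margin in the analysis section, about 79 events, and the usual approximation for the standard error with equal groups. That band lies wholly below 1, so the rules would disagree only when the pulsed field group had the lower observed recurrence rate. Since the point governs the confirmatory claim, it should be settled before the primary analysis.

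**What to change.** In the Statistical analysis section, replace "using a 1-sided test with alpha of 5" percent by: *a 1-sided alpha of 0.025, i.e. the upper limit of the 2-sided 95% confidence interval*, and say that it applies in both populations. Add the sidedness to the general sentence on alpha. The cost is one or two sentences and no patients, since the sample size was already calculated at this level.

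This change does not settle a separate matter. The sample size reproduces only if the margin, "with the noninferiority margin set to 20% comparing the 2 single-shot ablation technologies", is read as percentage points, while the analysis section uses a rate ratio of 1.2. With about 79 events and equal devices, power against 1.2 is about 13% at 1-sided 0.025 and 20% at 1-sided 0.05, so aligning alpha alone does not make the test adequately powered. The margin scale needs its own resolution.

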## Methods

### Study design

SINGLE SHOT CHAMPION (NCT05534581) is an investigator-initiated, randomized controlled (1:1), parallel, noninferiority, prospective, open-label phase 4 trial with blinded endpoint adjudication performed in 2 clinical centers in Switzerland. The objective of the SINGLE SHOT CHAMPION study is to assess the effectiveness and safety of the FARAPULSE PFA catheter compared with the Arctic Front cryoballoon for initial PVI procedure in patients with symptomatic paroxysmal AF. Considering that cryoballoon ablation is the established standard for PVI with single-shot ablation while the FARAPULSE PFA catheter represents a novel technology, this trial adopts a noninferiority design. The study flowchart is given in Figure 1.

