### Randomization

After 1:1 randomization, patients undergo PVI with either the FARAPULSE PFA catheter or the Arctic Front cryoballoon. To conceal treatment assignment, a restricted randomization method employing permuted blocks with randomly varying block sizes of 2, 4, or 6 is employed. Additionally, study centers stratify the randomization process. The allocation sequence is based on computer-generated random numbers and integrated into the database.

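### Randomisation is stratified by centre, but the primary log-rank test and rate ratio are unadjusted, so the deciding interval ignores the design, at a small cost

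*Protocol article*

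**What the plan says.** The Randomization section of the protocol article states that "study centers stratify the randomization process", with permuted blocks of 2, 4 or 6. Under Study design, the trial is "performed in 2 clinical centers in Switzerland", so there are two strata.

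Under Statistical analysis, for the primary comparison, "unadjusted survival curves are estimated by the Kaplan-Meier method and compared by log rank tests", and "Unadjusted rate ratios and confidence intervals for rate ratios are derived from Mantel-Cox models". The same section makes the upper limit of that rate ratio the deciding quantity: it must be one that "does not cross 20% (rate ratio of 1.2), using a 1-sided test with alpha of 5" percent. Centre is not mentioned in the primary analysis.

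The Sample size section uses a one-sided level of 0.025 and a margin written only as 20%, and also describes the criterion as a difference in cumulative incidence.

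**The concern.** When allocation is balanced within centre, the analysis should normally condition on centre. If it does not, and centre predicts recurrence, two things happen. The model-based standard error no longer matches the sampling variability of the estimate, because stratified allocation has removed the between-centre part of the arm imbalance. And a hazard-type ratio estimated without a prognostic stratum moves toward 1.

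In a noninferiority trial both matter, because the claim depends on where one confidence limit falls. A mis-sized interval changes the real error rate, and attenuation can change which side of the margin the limit lands on. The question is how much of each there is, and in which direction they net out.

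**Working it through.** **Inputs from the article.** Two centres; 1:1 allocation; 99 evaluable patients per group; expected primary event proportion 40%; one-sided 0.025 (Sample size); margin a rate ratio of 1.2 (Statistical analysis) or 20% (Sample size).

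**Input assumed.** The between-centre difference in recurrence. The article gives none, so centre hazard ratios of 1 to 3 are used, with equal-sized centres. At 40% overall control incidence, a centre hazard ratio of 2 gives centre incidences of 29.6% and 50.4%, and 3 gives 24% and 56%.

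**Reproducing the sample size.** Read 20% as percentage points, 40% against 60%. Implied ratio = ln(0.4)/ln(0.6) = 1.794. Freedman events = (1.960 + 0.842)² × (2.794/0.794)² = 97.2, rounded up to 98. At a mean incidence of 50% that is 196 patients, 98 per group, against the stated 99. Then 99/0.95 = 104.2, rounded up to 105, as stated. So the trial was sized for an implied ratio of 1.794, although the decision rule says 1.2. Both margins are checked below.

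**Attenuation (large-sample limit of the unstratified ratio).**

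| True within-centre ratio | Centre HR 1 | 1.5 | 2 | 3 |
|---|---|---|---|---|
| 1.2 | 1.200 | 1.198 | 1.194 | 1.185 |
| 1.0 | 1.000 | 1.000 | 1.000 | 1.000 |
| 0.8 | 0.800 | 0.802 | 0.804 | 0.811 |

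The movement is toward 1: zero at 1.0, and in the opposite direction below 1.

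**Standard error (6,000 simulated trials per scenario, true ratio 1.2).** Mean model standard error against the actual spread of the log ratio:
- Centre HR 1: unstratified 0.219 vs 0.218; stratified 0.219 vs 0.218.
- Centre HR 2: unstratified 0.219 vs 0.213 (about 3% too large); stratified 0.219 vs 0.218.
- Centre HR 3: unstratified 0.220 vs 0.206 (about 7% too large); stratified 0.220 vs 0.220.

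**Netting the two at margin 1.2.** The chance of a false claim is about Φ[(−1.96 × SE − shift)/SD], where shift is the log of attenuated over true ratio.
- Centre HR 2: shift = ln(1.194/1.2), about −0.005; (−0.430 + 0.005)/0.2125 = −2.00, giving 2.3%.
- Centre HR 3: shift = ln(1.185/1.2), about −0.013; (−0.431 + 0.013)/0.206 = −2.03, giving 2.1%.

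The simulation agrees. Unstratified vs stratified: 2.22% vs 2.43% (HR 2) and 2.22% vs 2.55% (HR 3). With no centre effect both are 2.53%. The Monte Carlo standard error of each rate is √(0.025 × 0.975/6000), about 0.2 points. At the one-sided 5% level in the Statistical analysis section: 4.90% vs 5.15%, and 4.85% vs 5.28%.

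**Chance of success at a true ratio of 1.0, margin 1.2, one-sided 0.025.** 12.2% vs 12.7% (HR 2) and 11.4% vs 12.6% (HR 3), a loss of 0.5 to 1.2 points. The intervals are equally wide; the unadjusted estimate simply varies less, and when success is unlikely, less spread means fewer successes.

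**At the implied margin of 1.794 (20,000 simulated trials per scenario).** False noninferiority, unstratified vs stratified: 2.8% vs 2.5% with centres at 30%/50%, and 3.3% vs 2.6% at 25%/55%. With no centre difference both are 2.7%. The average ratio is 1.77 and 1.72 unstratified, against 1.80 stratified. Attenuation grows with distance from 1, so here it slightly outweighs the over-wide standard error.

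**Difference scale.** Variance ratio, stratified to unadjusted = mean of p(1−p) over p̄(1−p̄).
- 30%/50%: [(0.21 + 0.25)/2]/0.24 = 0.958, a 4% reduction.
- 25%/55%: [(0.1875 + 0.2475)/2]/0.24 = 0.906, a 9% reduction.

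For a 20-point margin, unadjusted power = Φ[0.20/√(2 × 0.24/99) − 1.96] = 81.9%. Replacing 0.24 by 0.23 or 0.2175 gives 83.5% or 85.5%.

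**The case against.** An unadjusted log-rank test remains valid under stratified randomisation and is usually conservative. At the 1.2 margin that is what the figures show. The article also gives reasons to expect similar centres: one fixed procedure per device, a central monitor core laboratory and one blinded events committee. No centre recurrence rates are given, so every size above rests on assumed gaps. All of this stands, and it makes the point minor.

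On the ratio scale, stratifying does not reliably add power. At margin 1.794 and a true ratio of 1.0 the unadjusted analysis does slightly better: 73.5% vs 73.0% (30%/50%) and 75.0% vs 73.9% (25%/55%). That also stands; the precision argument belongs to the difference scale.

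It may be said that centre stratification is a matter for the analysis plan, which is not shown. That holds for supportive analyses, and their absence is not counted here. It does not hold for the primary analysis, which the article explicitly fixes as unadjusted.

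A reader might infer something stronger: that leaving out centre biases the trial toward declaring noninferiority. The documents do not support this. The pull is toward 1, which helps the claim only when the true ratio exceeds 1. At the stated margin of 1.2 the over-wide standard error more than offsets it. A small excess appears only at 1.794, a ratio that the article never states.

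**Conclusion.** The mismatch is real and written in the text: the allocation uses centre and the deciding interval does not. The consequence is a slightly miscalibrated interval if the centres differ, not a systematic advantage for the new device. Under assumed centre hazard ratios of 2 to 3, the false-claim rate is about 0.3 points below nominal at margin 1.2, or roughly 0.3 to 0.7 points above the stratified analysis at the implied 1.794. The centre-stratified analysis stays close to 2.5% under both readings, which is the best reason to prefer it while the margin is unresolved.

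This is a minor alignment point. It is much smaller than the conflict between the two margins: a ratio margin of 1.2 needs 4 × 7.85/(ln 1.2)², about 945 events, against about 79 expected (40% of 198).

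**What to change.** Before unblinding, state that the primary log-rank test and the Mantel-Cox rate ratio with its interval are stratified by centre. If a Kaplan-Meier difference at day 365 is used for the decision, combine the centre-specific differences with weights. Keep the unadjusted result as a named sensitivity analysis, and apply the same rule to the time-to-event secondary endpoints.

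The cost is wording only: no extra patients or data. With two strata there is essentially no penalty if the centres turn out alike; in the simulation without a centre effect the mean standard errors were 0.2189 unstratified and 0.2191 stratified. Fixing the choice now also prevents a later selection between two results that could fall on either side of the margin.
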